#### Client variables and measures

Secondary analyses will explore whether the rating method is less accurate for subsets of the population. We considered brief tests of literacy, English proficiency, or executive functioning, but because they are orally administered and require assessor training, they are not feasible for clinicians to administer and may cause client discomfort. Instead, we will use variables that capture related and correlated factors including traumatic brain injury and comorbidity (via clinician report) and other demographics via self-report.

#### Client skill

As with our previous work, we will calculate scores for client skill (ability to complete homework sheets; client worksheets will be rated on the same measure). We will report the range of abilities of our sample and use the scores as a covariate in analyses of the association between quality and outcomes.

#### CBT fidelity

We will use the Cognitive Therapy Rating Scale (CTRS) [60, 61], the “gold standard” observer rating scales for CBT for all sessions, and for CPT sessions, we will also use the CPT observer rating scale [21]. Trained postdoctoral fellows and advanced graduate students will rate 10% of the session recordings. They will overlap on 10–15% of these sessions to facilitate reliability analyses. ICCs for observer ratings in our previous studies using these instruments have been high, ranging from .79 to .84 ([45]; Monson et al.: A randomized controlled trial of training and consultation methods to deliver cognitive processing therapy for posttraumatic stress disorder: Impact on patient outcomes, submitted).

#### Clinician and organization variables: covariates

Additional measures will be collected at baseline to explore organization- and clinician-level moderating effects on the association between quality on clinical outcomes (Clinician Demographic Characteristics and Experience Questionnaire, Evidence-Based Practice Attitudes Scale, and Perceived Chrematistics of Interventions and the Implementation climate Assessment) [62–64]. We will assess characteristics that may contribute to quality outcomes [65]: degree, years of experience, gender, age, and prior CBT/ EBPT training.

#### Interviews and assessment of stakeholder perspectives

We will use brief rater surveys and stakeholder interviews (raters, clinicians, 15–20 clients per system, policymakers, and administrators) in each system to assess relevant constructs of the Consolidated Framework for Implementation Research (CFIR) [66] such as perceptions of relative advantage, complexity, design quality/ packaging, readiness for implementation, and inner and outer context factors that might influence implementation. We will assess time required for rating, identify roles that would most likely serve as quality assessors in the different systems (e.g., supervisor, quality assurance staff), assess hourly costs associated with each clinical/quality assessor role, and assess time required for transmitting the worksheets for app vs paper formats. We will assess productivity demands and other demands and responsibilities that may impact use of the assessment strategies. We will follow up to assess perspectives on the contribution of client, clinician, and system characteristics to any variance in quality scores that is identified in our analyses. We will also assess perspectives on use of the mobile apps vs. paper forms, satisfaction, suggestions for refinement, and perceived adequacy of information in the quality measures.

#### Raters and scoring

We will apply the rating system that is refined in the first phase of the study to worksheets that are collected during the entire course of the study. The scoring rules (including decision rules for each session) and scoring algorithms are embedded in an electronic database for app and paper copies. The cadre of raters will include postdoctoral fellows from each system and bachelor’s level research assistants, and some are able to rate sessions and worksheets in Spanish. They will be trained to use the measure and to become familiar with all decision rules, and new decision rules may be identified during this training process. These sessions will be evenly distributed between raters. A subset (10%) will be rated by a second time (1 week after the first rating) to assess test-retest reliability. Furthermore, participating systems will nominate one person (whoever would be in a position to monitor quality) to receive brief training and rate 10 sessions to determine feasibility of training system/clinic-level quality monitors. They will be interviewed regarding potential for implementation within their setting. A randomly selected subset (20%) of the worksheets will be rated by CBT experts and compared with our raters. To score the adherence checklists embedded in the clinical notes, we will score the proportion of CBT elements that are checked off by clinicians.

### Analytic strategy

We will conduct the following analyses:

#### Reliability

We will examine correlations between the subset of worksheets that are rated twice to examine test-retest reliability. Next, we will compute estimates of internal consistency reliability for hypothesized CBT domains (e.g., identifying thoughts and feelings, cognitive restructuring, behavior planning and tracking) in the form of Cronbach’s alphas and retain domains with an alpha of .70 or above. We will calculate intraclass correlations (ICCs) for the total measure and for each content domain, using a random effects model to estimate the reliability of rater judgments [67]. Per established conventions and prior research [68], we will apply a minimum criterion ICC = .60 (“good”) [69] to indicate acceptable agreement. We will also compare bachelor’s level raters’ scores to expert rater scores to assess the degree of agreement, to determine a level of expertise required for rating.

#### Concurrent validity

We will compare our strategy to the “gold standard” fidelity measure and clinical progress notes alone. We predict that ratings on our quality monitoring method will be highly correlated with existing [3, 17] objective and reliable observer ratings and that they will be more accurate than the ratings based on the checklists embedded in the clinical notes alone [2, 21, 70, 71]. We will examine Spearman rank correlations [72] between our method and independent observer ratings for the overall measure, for each subscale and for conceptually corresponding items. Further, we will conduct cross-validation borrowing the idea of checking internal validity of prediction models in statistical learning [73].

#### Factor analysis

We will conduct an exploratory factor analysis to examine the factor structure of items within each worksheet. It is possible that quality may differ across different elements/domains of CBT, but it is also possible that CBT quality is better represented as a composite variable (some areas are of higher quality than others and that summing across them still provides good information about overall quality). Thus, we will explore the possibility of multiple factors or domains (e.g., cognitive restructuring), and will also evaluate the extent to which the components are best represented as a latent variable, that is, a general tendency to provide high-quality CBT that is reflected in high scores across different CBT components.

#### Clinical outcome predictions

We expect that clients whose sessions receive higher quality ratings will exhibit larger decreases in symptoms compared to clients whose sessions had lower ratings. Based on previous research suggesting that it is important to assess fidelity in early sessions to avoid temporal confounds between process variables and outcomes [22, 68, 74, 75], we expect that quality in earlier sessions will more accurately reflect the contributions of session quality and clinician skill (rather than client factors) than that in later sessions. Primary analyses will focus on quality in sessions 1–6. We will cross-validate prediction models as a way of checking internal validity (generalization error).

#### Analyses

We will first examine distribution of key variables for skewness, variability, and outliers and apply appropriate transformation or other strategies to address non-normality (e.g., robust estimation procedures) as necessary. Symptom scores from instruments that reflect the target problem for each client (e.g., depression, anxiety, or PTSD) will be standardized, and the standard scores will be used as the dependent variable (DV). We will also conduct secondary analyses with the measures for each target problem and with the functioning measure as DVs. The study will produce hierarchical data with repeated measures (Level-1) nested within clients (Level-2) nested within clinicians (Level-3). To evaluate change in client outcomes, we will conducted multilevel regression (i.e., mixed-effects regression, hierarchical linear modeling) growth curve analysis, which offers numerous strengths for analyzing change in nested data, including efficiency in handling missing data, powerful and accurate estimation procedures adjusting for clustering, and modeling flexibility (e.g., allows for the inclusion of continuous or categorical, time-invariant or time-varying covariates and predictors). We will employ strategies to check the sensitivity of analysis results due to missing data (e.g., pattern mixture modeling) [76]. We will analyze the intent-to-treat sample [77] and completer samples. First, multiple unconditional change models (i.e., change without predictors) will be evaluated to determine the most reliable and powerful way to analyze change (e.g., linear or non-linear change; modeling time as time since baseline or as session number) and determine the most appropriate variance-covariance structure, considering, among others, the autoregressive structure.

The first set of multilevel regression analyses will evaluate trajectories of outcomes over the entire course of therapy or over the course of several sessions. We will examine the influence of potentially significant covariates (e.g., baseline scores, setting, veteran status, client skill, and other clinician, setting, or client characteristics) and include in exploratory analyses. Given the small number of systems, the system will be entered as a potential covariate to assess and adjust for its influence, but we will conduct an exploratory analysis with the system entered at Level-4.

The next multi-level regression analyses will examine the session-by-session associations between quality and symptoms. Lagged multivariate models will allow for the inclusion of two outcomes (quality and symptom change) in the same model [78–80]. Evaluation of the cross-lagged paths will provide information about temporal precedence in the relationship between the two variables across time. We will also account for overall increases and decreases in the model by including time as a predictor of each outcome.

We will next determine whether the different quality measures or worksheet formats differ in terms of how strongly they are associated with subsequent symptom change. Since clients will be randomized into worksheet format (app vs paper form), a dichotomous variable with paper form as the reference will be entered at Level-2 in the analyses described above to examine whether format predicts symptom change. We will explore potential interactions with target problem (PTSD, depression, anxiety). We will examine and compare the effect sizes and the proportion of variance accounted for by the worksheet measure and the adherence checklist. We will also compare them for app vs. paper form worksheets. A medium or large effect would be clinically meaningful in the context of the pragmatic goals of this project, particularly because the reliable change index for each of our outcome measures corresponds to a large effect size [48, 49, 58]. On the other hand, if associations with outcomes differ only slightly, we would recommend selection of a quality assessment strategy based on specific programs’ needs or goals.

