### Data collection and research strategy summary

After the development of the scoring system, we will prospectively collect data in a variety of settings, with clinicians (*n* = 120) who have varying levels of experience and expertise with CBT. We will collect data on clinician, client, and organizational characteristics that may impact the assessment of psychotherapy quality. We will collect worksheets, symptom measures, clinical notes with checklists of CBT strategies embedded within them, and therapy session recordings for participating clients. They will be provided to the investigators using secure, Institutional Review Board (IRB)-approved modes of data transmission that have been used successfully in our previous research [44–47].

Participating clients will be randomized into one of two different worksheet formats—app version or paper form (content is the same, mode of completion and data transmission differs). Raters will access the copies of the worksheets, or the mobile app dashboard, and score the worksheets. Clinicians, administrators, supervisors, and clients will be interviewed to assess perceptions of the quality assessment strategies and to determine feasibility, and these data will be analyzed using qualitative strategies.

The variety of worksheets and data capture sources (apps, paper forms) will allow assessment of clinician and client preferences, the degree of detail and completion required for accurate quality assessment. This strategy will allow us to answer several questions through our statistical and qualitative analyses. Analyses will be conducted to answer questions and test hypotheses regarding (1) the reliability and factor structure of the measure, (2) associations between the quality measure and subsequent symptom change (the primary outcome), (3) the concurrent validity of the measure, (4) whether the measure performs better than adherence checklists embedded in clinical notes, (5) whether different formats (apps vs. paper forms) have different concurrent or predictive validity, and (6) the feasibility, burden, satisfaction, and time requirements for the worksheets vs. the adherence checklists.

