#### Sample size justification and power calculations

In light of the project’s emphasis on the development of pragmatic measurement strategies that predict changes in the target problems, we powered the study to test for predictive validity. Calculations of a design effect (measure of how the design effects the standard error of the parameters) [81, 82] accounted for clustering. We computed ICC with repeated observations of clients at the clinic (*r*_*pb*_ = .01), clinician (*r*_*pb*_ = .01), and client (*r*_*pb*_ = .10) level in our prior research, assuming three clients per clinician, and six clinicians per cluster, and six observations per client, yielding a design effect of up to 2.04. We based the estimated number of observations per client to conservatively account for potential 37% client-level attrition and missing data during the treatment. For the growth curve analyses to assess whether the quality measure predicts symptom change (our primary analysis), the probability of a type 1 error (alpha) at two-tailed .05 power exceeds .80 for an effect size of *r* = .30, which corresponds with small-to-medium effects of fidelity on symptoms in prior CBT fidelity research [68, 83]. We also projected a sample size to be sufficient to conduct separate analyses and test for interactions with disorder (PTSD vs. depression vs. anxiety), app vs. paper form, and other variables of interest, and detect an effect size of .50, a medium effect.

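### The model term given for app versus paper predictive validity tests whether format predicts symptom change, not whether the quality–symptom association differs by format

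*Protocol article*

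**What the plan says.** In *Data collection and research strategy summary*, the fifth question to be answered is "whether different formats (apps vs. paper forms) have different concurrent or predictive validity". In *Analyses*, the paragraph on the predictive half of that question sets out to determine whether the quality measures or "worksheet formats differ in terms of how strongly they are associated with subsequent symptom change".

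The next sentence gives the model term. Because clients are randomised to format, a dichotomous variable with paper as reference "will be entered at Level-2 in the analyses described above to examine whether format predicts symptom change".

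Three further statements bear on the point:

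- The only interactions named in that paragraph are with disorder: "We will explore potential interactions with target problem (PTSD, depression, anxiety".
- For the quality measures, the plan says "We will examine and compare the effect sizes and the proportion of variance accounted for by the worksheet measure and the adherence checklist". For format it adds "We will also compare them for app vs. paper form worksheets".
- *Sample size justification and power calculations* says the sample should suffice for separate analyses, to "test for interactions with disorder (PTSD vs. depression vs. anxiety), app vs. paper form, and other variables of interest", and to "detect an effect size of .50, a medium effect".

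The concurrent half of the question is handled in *Comparisons of quality measures (worksheet vs. adherence checklists) and worksheet formats*. There a Fisher r-to-z test compares the formats on their correlation with observer ratings. It does not involve symptoms.

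**The concern.** Each client uses one format. A difference in predictive validity is therefore a difference between arms in the slope of later symptoms on worksheet quality, that is, a quality-by-format interaction. The term written down answers another question: whether clients assigned to the app improve more or less than clients assigned to paper.

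The two can come apart in both directions. Format may have no effect on symptoms while the worksheet score predicts outcome better on one format. Format may also shift symptoms while the score predicts equally well on both. If the format coefficient were reported as the answer to question 5, a real difference in validity could be missed, or a treatment effect of format could be read as a difference in validity.

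**Working it through.** **1. The two estimands.** Let F be format (0 paper, 1 app), Q worksheet quality, T time and Y the standardised symptom score. Leaving out random effects and covariates, a growth model that carries both questions is

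Y = b0 + b1·T + b2·F + b3·F·T + b4·Q + b5·Q·T + b6·Q·F + b7·Q·F·T.

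The stated purpose, whether format predicts symptom change, corresponds to b3. The stated aim, whether the association of quality with symptom change differs by format, corresponds to b7. In the session-by-session model it corresponds to the coefficient of lagged quality × format. No value of b3 determines b7.

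**2. The plan's own power figure.** It claims power above .80 for r = .30 at two-tailed .05. Inputs are 360 clients and the stated design effect of up to 2.04. Power = Φ(√(n − 3)·atanh(.30) − 1.96).

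- n = 360/2.04 = 176: √173.5 × .3095 − 1.96 = 2.12, power .98.
- n = 360 × .63/2.04 = 111: √108.2 × .3095 − 1.96 = 1.26, power .90.

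The claim reproduces. It concerns the overall quality–symptom association, not a difference between formats.

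**3. What each term detects.** The documents give no slopes by format, so the slopes and shifts here are assumptions. Single-level model: Y = g·F + b(F)·Q + e, with Q standard normal, residual SD .95, half the clients on each format (1:1 is assumed), 3,000 data sets per case, ordinary least squares, two-sided 5%. The n of 176 is 360/2.04.

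| Slope paper / app | Format shift g | n | Format term rejects | Quality × format rejects |
|---|---|---|---|---|
| -.45 / -.15 | 0 | 360 | 4.3% | 83% |
| -.45 / -.15 | 0 | 176 | 5.7% | 54% |
| -.30 / -.30 | -.30 | 360 | 84% | 4.9% |
| -.30 / -.30 | -.30 | 176 | 56% | 4.8% |

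A hand check of the interaction column: the standard error is about 2 × .95/√n, which is .100 at 360 and .143 at 176. A slope difference of .30 then gives Φ(.30/.100 − 1.96) ≈ .85 and Φ(.30/.143 − 1.96) ≈ .55, in line with the simulation.

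**4. What a comparison without an interval leaves open.** For two independent correlations the 95% half-width on the Fisher z scale is 1.96·√(2/(n − 3)), with n per arm.

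- 180 per arm: 1.96·√(2/177) = .21.
- 88 per arm (180/2.04): 1.96·√(2/85) = .30.

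Chance differences between formats of that size are therefore ordinary. The same paragraph of *Analyses* bases a recommendation on whether associations differ only slightly. The 37% loss is not applied here, because the plan builds it into the number of observations per client.

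**The case against.** The strongest reply is that the plan does address predictive validity by format, in places other than the Level-2 sentence. Effect sizes and variance explained are to be compared for app and paper. The sample size section, which is about predicting symptom change, plans interaction tests with format, and a quality-by-format term is the natural reading. The paragraph in *Analyses* also signals that differences will be judged by size, so the lack of a p-value is not in itself a fault. A Level-2 variable in a multilevel model can predict the quality slope as well as the intercept, and a condensed article need not print the equation.

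Much of this stands. A reader might infer that the format indicator is the plan's whole provision for this question. The documents do not support that. A reader might also infer that the randomisation or the main result is undermined, and that is not supported either: the primary analysis concerns the overall association, the concurrent-validity half of question 5 has a formal test, and the abstract gives the randomisation other purposes, namely client and clinician experience and how well format reflects fidelity.

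What does not stand is the broad reading of the Level-2 sentence. The article gives the term, its level, its reference category and its purpose, and that purpose is the effect of format on symptom change. The size comparison has no interval by which to judge it. The sample size section does not say which variable interacts with format, and the .50 it quotes has no stated metric. If the quality-by-format term was meant, the two sections have yet to be joined.

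**Conclusion.** The point holds for the predictive half of question 5, as a mismatch between the stated question and the stated model term. It goes beyond omitted detail, because the term that is named estimates something else. The descriptive comparison and the undefined interaction in the sample size section soften the gap without closing it.

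The mismatch itself follows from the text and needs no assumption. The rejection rates do rest on assumptions: slopes of -.45 and -.15, a shift of -.30, 1:1 allocation and a single-level model in place of the planned three-level one. The near-alpha rate for the format term is a consequence of simulating no mean format effect. It shows that the two terms differ, not how much this trial would lose. Nor do the figures show that the sample is too small, since the documents give no target for the format difference.

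This is a secondary question of moderate importance. The primary analysis is unaffected.

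**What to change.** In *Analyses*:

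- Name the quality-by-format term as the test of differential predictive validity: quality × format × time in the growth model, and lagged quality × format in the session-by-session model, each with its lower-order terms.
- Report the quality slope for each format, with a confidence interval for their difference, alongside the planned comparison of effect sizes and variance explained.
- Keep format × time as a separate question, labelled as whether format affects symptom change.

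In *Sample size justification and power calculations*, say that the format interaction is quality by format, and give the metric of the .50. Any power illustration for it should be labelled as resting on assumed slopes.

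The cost is wording and one added term per model. No new data are needed. Making the change before the data are analysed avoids the appearance of a model chosen after the fact.

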Another advantage of using worksheets to assess fidelity is that CBT worksheets are accessible and easily transmitted. They are available in paper form and through mobile technology that is accessible to people with disabilities (e.g., hearing- or vision-impaired). The majority of adults in advanced economies, and over half in emerging economies, own smartphones [38, 39]. Mobile applications (apps) are increasingly being used in CBT sessions, making transmission for real-time quality assessment feasible. Worksheets have been adapted for lower levels of literacy, multiple languages, traumatic brain injury, and other factors. Thus, it is possible to tailor worksheets that fit client needs and tailor strategies for collection and rating for different settings. However, the quality and feasibility of data collection may vary across formats and settings. For example, app worksheets may be more legible than handwritten data but may also be briefer or less detailed due to difficulties in typing on a phone. We propose to refine and test a unique method of assessing treatment quality through worksheets generated through routine clinical procedures. Specifically, we aim to (1) develop a scalable general CBT quality measure based on work samples rather than self-report or observation and (2) to evaluate the reliability, validity, and feasibility of different strategies for collecting these materials (e.g., mobile apps vs. paper worksheets).

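### The randomised effect of worksheet format on symptoms is to be read from models that hold, or may hold, worksheet scores measured after randomisation; a format model without them should be stated

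*Protocol article*

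**What the plan says.** All references are to the protocol article.

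- **Randomisation.** Under *Recruitment and informed consent*, clients are allocated to app or paper after consent and before any worksheet is collected.
- **Format analysis.** Under *Analyses*, the format indicator (paper as reference) is justified by the randomisation and "will be entered at Level-2 in the analyses described above to examine whether format predicts symptom change".
- **Lagged models.** These come just before that sentence: "Lagged multivariate models will allow for the inclusion of two outcomes (quality and symptom change) in the same model". Quality is in them by construction.
- **Growth curves.** *Sample size justification and power calculations* describes their purpose: "For the growth curve analyses to assess whether the quality measure predicts symptom change (our primary analysis". *Clinical outcome predictions* adds: "Primary analyses will focus on quality in sessions 1–6".
- **First set of regressions.** Under *Analyses*: "The first set of multilevel regression analyses will evaluate trajectories of outcomes over the entire course of therapy or over the course of several sessions". Quality is not named there. Client skill is listed among the covariates that may be examined.
- **Client skill.** It is scored from homework worksheets on the same measure. The *Client skill* section says the team will "use the scores as a covariate in analyses of the association between quality and outcomes".
- **Possible effect of format on the sheet.** The *Background* says app entries may be easier to read than handwriting, but "may also be briefer or less detailed due to difficulties in typing on a phone".

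**The concern.** Randomisation protects the comparison of symptoms between app and paper clients as allocated. That protection does not extend to a comparison made at equal values of something measured later that allocation can influence. Worksheet quality is such a variable, because it is rated from the sheet whose format was randomised. Client skill is another, because it is rated from homework sheets on the same measure.

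Two errors can follow when either score is in the model that yields the format coefficient:

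1. **A recording difference becomes a symptom effect.** Suppose app sheets score lower only because less is typed. An app client and a paper client with the same score then differ in true quality, the app client having received the better session. The app appears to improve symptoms. The sign reverses if the app raises scores.
2. **A real effect disappears.** If format truly changes the quality of the work and thereby symptoms, adjusting for quality removes the effect the sentence sets out to examine.

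The article says where the indicator is placed and what it is meant to answer, so the point does not rest on detail left to a fuller plan.

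**Working it through.** **The plan's own figure.** The article claims power above .80 at r = .30, two-tailed alpha .05. By the Fisher approximation, power = Φ(atanh(.30)·√(n − 3) − 1.96):

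| n | Power |
|---|---|
| 360 | .9999 |
| 360/2.04 = 176.5 | .983 |
| 360 × .63 = 226.8 | .996 |
| 360 × .63/2.04 = 111.2 | .896 |

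The claim reproduces, taking the design effect of 2.04 as stated, and is not disputed here.

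**Inputs for the format question.** From the article: 360 clients and a planning effect of .30. Assumed: 1:1 allocation (180 per arm; the ratio is not stated); direction of the slope (better quality, fewer symptoms), so β = -.30; no true effect of format; and a shift δ of the rated score due to format alone of 0, -0.2, -0.5 or -0.8 SD of true quality. The article gives no size for δ.

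**Algebra.** Let q be true quality, symptoms y = βq + error, and the rated score s = q + δ·app. Substituting q = s − δ·app gives y = βs − βδ·app + error. The format coefficient with s in the model is therefore −βδ although the true effect is zero. At δ = -0.5 it is −(−.30)(−0.5) = -0.15 SD. If the score has reliability .70, the slope on s becomes -.30 × .70 = -.21 and the coefficient -0.105.

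**Rejection rate by hand at δ = -0.5, error-free score.** Residual SD = √(1 − .09) = .954. Variance inflation from the app–score correlation = 1 + 0.25 × 0.5² = 1.0625. SE = .954 × √(2/180) × √1.0625 = .104. z = .15/.104 = 1.45, and Φ(1.45 − 1.96) = .30.

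**Simulation, 4,000 runs per cell, one observation per client.** Each cell gives the mean format coefficient in SD and the rejection rate at nominal 5%.

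| δ | Score in model, n = 360, error-free | n = 360, reliability .70 | n = 226 (37% loss), error-free | n = 226, reliability .70 |
|---|---|---|---|---|
| 0 | 0.00, 5% | 0.00, 5% | 0.00, 5% | 0.00, 5% |
| -0.2 | -0.06, 9% | -0.04, 7% | -0.06, 7% | -0.04, 6% |
| -0.5 | -0.15, 30% | -0.11, 18% | -0.15, 21% | -0.10, 12% |
| -0.8 | -0.24, 59% | -0.17, 35% | -0.24, 41% | -0.17, 24% |

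With format alone in the model, the coefficient is 0.00 and rejection is about 5% in every cell (4% to 6%).

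**Repeated-measures check.** A random-intercept model with 360 clients × 6 sessions and δ = -0.5 gave -0.146 with 44% rejection when the score was included, and 0.008 with 2.5% when it was left out. It rests on 120 runs, so its rates are rough.

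**The opposite error.** If format lowers true quality by 0.5 SD, the real total effect is (−.30)(−0.5) = +0.15 SD. With an error-free score in the model it falls to 0.00; at reliability .70 it falls to .15 − .21 × 0.5 = +0.045. Simulation gave 0.001 and 0.045.

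**Limits.** The simulations concern symptom level and carry no clinician clustering or format × time term. They show the mechanism and its order of size, not the exact error rate of the planned model.

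**The case against.** The case on the other side has real force.

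- **The first set of regressions does not name quality.** Adding format to a trajectory model without quality would be close to the right analysis, and the text does not exclude it. This stands: a reader might infer that every format model in the plan holds quality, and the article does not say so. But it names no format model that leaves quality out, two other sections make quality the predictor in the primary growth curves, and the lagged models hold it explicitly.
- **In the joint lagged model quality is also an outcome**, so a total effect could be recovered if format entered both equations and the paths were combined. Likewise, if session quality were centred within client, a constant shift would drop out. Both are possible, but the article describes neither and reads the indicator itself.
- **A shift is only a possibility.** A reader might infer that the protocol expects the app to lower scores. It mentions better legibility and shorter entries side by side, gives no size, and states that content is the same in both formats. This stands, and without a shift there is no bias.
- **Client skill may never reach the format model.** Its own section ties it to the quality–outcome analyses, and the covariate list is exploratory. This stands; the risk is that nothing keeps it out.
- **The effects are small against the plan's yardstick.** All false coefficients above lie below the .50 that the sample size section sets for format and interaction analyses. This also stands, but a false positive would still be reported, and a real effect through quality could be missed.

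**Conclusion.** The point holds as a defect in a secondary analysis. Where worksheet quality or client skill is in the model, the format coefficient answers a different question from the one stated, and randomisation does not protect it. The distortion is −βδ: about 0.04 to 0.06 SD for a 0.2 SD shift, 0.11 to 0.15 SD for 0.5 SD and 0.17 to 0.24 SD for 0.8 SD, at reliability .70 and 1 respectively, and zero with no shift. These sizes rest on assumed shifts, a slope of -.30 and 180 clients per arm; attrition lowers the false rejection rates but not the bias.

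A reader might go further and conclude that the trial's randomised comparison as a whole is lost. The documents do not support that. The format contrasts on agreement with observer ratings, on predictive validity, and on burden and satisfaction are unaffected, and the predictive-validity question needs quality in the model. The primary analysis, quality as a predictor of symptom change, is not touched by this point.

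**What to change.** 1. State that the effect of format on symptom change is estimated in the intent-to-treat sample, in the multilevel growth model with format, time, format x time and pre-randomisation covariates only (for example baseline score, setting, veteran status, target problem). Say explicitly that worksheet quality and client skill are left out, and that format x time is the term read as the effect on change.
2. Report the app–paper difference in mean quality score as a separate randomised contrast. It also shows whether a shift exists.
3. Keep the models with quality and the format x quality interaction for the question of whether predictive validity differs by format. Add that the format main effect in those models is not read as the randomised effect.

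The cost is one extra model and a few sentences in the analysis section. All the data are already to be collected, and neither the sample size nor the primary analysis changes.
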